### Randomisation/blinding

Stratified randomisation with blocks of four or six will be used according to (i) the presence or absence of diseases that increased cardiovascular risk and required a lower BP target (<130/80 mmHg) (including DM, history of cardiovascular diseases, history of chronic kidney disease) and (ii) the number of anti-HT medications (<3 or ≥3) because the number of medications affects medication adherence and the likelihood of maintaining optimal BP control [17]. The randomisation sequence will be generated by an independent statistician, using the statistic programme Random Allocation Software, version 1.1.0, printed out, and sealed in light-opaque envelopes, which will only be opened by the research assistant after a participant’s eligibility is confirmed and the consent form is signed. Due to the nature of the intervention, blinding the investigators, participants, and healthcare providers will be infeasible after randomisation. However, the independent statisticians who will conduct the analysis will remain blinded.

### Intervention/control arm

#### Intervention arm: telemedicine

Patients will be: (i) given a validated HBPM device (ORMON HEM-7120) with appropriate cuff size, (ii) taught the HBPM technique, and (iii) taught to record HBPM readings using the HealthCap mobile app on their smartphones.

Participants randomised to intervention will be reminded to take dual BP readings in the morning and evening for 1–2 weeks before the index consultation. These BP readings will be automatically sent to a computer at the clinic. When the HBPM mean is optimal (i.e. <135/85 mmHg or <130/80 mmHg [for patients with cardiovascular diseases, renal diseases, and DM]), other parameters will be checked using an online questionnaire, and responses will be screened by the physicians, including (i) self-reported good drug compliance and no drug side effects, (ii) absence of symptoms of complications (i.e. chest pain and hemiplegia), (iii) absence of hyperglycaemia and hypoglycaemia symptoms (only for patients with DM), and (iv) no other health complaints that need consultation. When all the answers are negative, medications will be delivered to the patient by tracked mail, and the index physician appointment will be deferred for 16–18 weeks (the usual follow-up period for these patients is now 16–18 weeks). The index consultation will proceed as scheduled if BP is suboptimal or any of the safety questions screen is positive. HealthCap has an automatic feedback function. For example, if BP is dangerously high (i.e. SBP ≥ 180 or DBP ≥ 110 mmHg), HealthCap will recommend a recheck and advise attendance at the emergency department if BP remains elevated (Fig. 1).

**Fig. 1 Fig1:**
[figure not shown]
Flowchart for patients in the intervention (telemedicine) group. *Safety questions included the following: (i) self-reported good drug compliance and no drug side effect, (ii) absence of symptoms of complications (i.e. chest pain and hemiplegia), (iii) (only for patients with DM) absence of hyperglycaemia and hypoglycaemia symptoms, and (iv) no other health complaints

HealthCap may also enhance self-management because it automatically reminds patients to measure BP regularly (every 1–2 weeks), provides feedback on patients’ BP values (compared to the threshold of elevated BP), and links to online healthcare educational resources.

#### Control arm

Participants will continue receiving routine care, including anti-HT drug prescriptions, from their regular physicians. In HK, patients with well-controlled HT are routinely seen every 16–18 weeks. Participants will also be given the same HBPM devices and taught the techniques. This is necessary because HBPM is a secondary outcome. According to the HK guidelines, all patients with HT are advised to regularly monitor their home BP, which can be considered as usual care [16]. However, the patients will not be taught any BP measurement algorithm (such as that used in the telemedicine group). They will also be asked not to download or use any new HT mobile apps during the study period. Additionally, the research assistant will ask if patients use any HT mobile apps at the baseline. The research assistant will then monitor and record the use of any new HT mobile apps at 6 months and 12 months.

In HK, all citizens have unlimited access to GOPCs and emergency departments for health problems. These services will not be limited for any participants in the current RCT. All participants are advised to seek medical help if BP becomes dangerously and persistently high (i.e. SBP ≥ 180 or DBP ≥ 110 mmHg) or in case of any suspected medical emergencies.

### Criteria for discontinuing or modifying allocation

Participants are encouraged to adhere to their assigned allocation as closely as possible. If any of the answers to the safety questionnaire are positive or the mean BP value from 7-day HBPM is suboptimal, the patient in the intervention group will receive usual doctor consultation. This consultation is part of the intervention and does not constitute a modification of allocation. Although there are no criteria for allocation modification, participants may withdraw from the study at any time if they choose to.

### Strategies to improve enrolment and adherence to interventions and follow-up

The recruitment rate will be regularly monitored. A trained research assistant will remind participants about adherence to interventions (e.g. 7-day home BP readings and filling in the safety questionnaire before index consultations in the HealthCap arm). Moreover, participants will be given supermarket coupons after they complete data collection at each timepoint (i.e. baseline, 6 months, and 12 months) to compensate the time and travelling cost, and to reinforce the patient adherence to the trial and data collection.

### Relevant concomitant care permitted or prohibited during the trial

Patients in the control group will be asked not to download or use any new HT mobile apps during the study period. There is no other specific concomitant care administered nor prohibited during the trial.

### Outcome measures

#### Primary outcome: daytime ABPM BP at 12 months

ABPM is the reference standard for BP measurements because of its superior reproducibility and predictability of cardiovascular outcomes [13, 14]. Mean daytime SBP will be the primary outcome of the RCT. SBP instead of DBP will be our primary outcome because SBP is more predictive of cardiovascular events than DBP, especially in the elderly [18]. WatchBP O3 (Microlife AG, Switzerland) has been validated by multiple HT societies (www.stridebp.org) and will be used in the current RCT. ABPM will be conducted in accordance with international guidelines (including the use of the non-dominant arm and appropriate cuff size) [19]. BP will be measured every 30 min for ≥24 h, and patients’ sleep diary will define the sleep duration. The readings will be considered valid if there are >70% valid readings overall, >20 valid awake, and >7 valid asleep BP readings in 24-h intervals [19]. Furthermore, erroneous and physiologically impossible BP readings are excluded (i.e. SBP outside the range of 50–240 mmHg and DBP outside the range of 40–140 mmHg) [19].

#### Secondary outcomes

Secondary outcomes will include variables related to other BP parameters, patient treatment adherence and self-efficacy, and health service utilisation. All secondary outcomes will be collected at baseline, 6 months, and 12 months unless specified otherwise. Acceptability will be further assessed by patient and physician interviews.

Blood pressure: This will include ABPM parameters (24-h/daytime/nighttime SBP and DBP) at 6 months and other ABPM parameters at 12 months (24-h/nighttime SBP/DBP and daytime DBP).

Furthermore, 7-day HBPM SBP/DBP will be measured using a validated device (ORMON HEM-7120; www.stridebp.org). Patients will be asked and reminded by the research assistant to measure dual readings in the morning and evening for 7 days in accordance with the local HT guidelines [16]. The mean SBP/DBP from the last 6 days will be used for analysis (BP readings from the first day can be higher due to anxiety, which is in accordance with local and international guidance) [12, 16]. This measurement algorithm was feasible and acceptable in our pilot RCT [9]. The minimal number of HBPM readings required for valid BP estimation is ≥12 BP readings [12]. HBPM may be more acceptable than ABPM in some patients whose sleep is disturbed by the ABPM or who have allergic reactions due to prolonged exposure to ABPM measurement cuffs [20]. Inclusion of HBPM as our secondary outcome will ensure successful out-of-office BP measurements in these patients.

Although less predictive of cardiovascular outcomes and less reproducible, office SBP/DBP will be collected at baseline and 12 months because office BP is still widely used in clinical practice. Various office BP devices are used in GOPCs and have been validated and maintained by the HK Hospital Authority. Measurement of office BP in GOPCs follows the HK primary care guidelines [16].

Health service utilisations and cost (collected at 12 months): Resource utilisation during the study period (including GOPC visits, emergency department visits, and hospitalisation) will be retrieved from the computerised clinical management system (CMS), and visits to private healthcare sectors, including private clinics and hospitals, will be self-reported. The number and types of anti-HT drugs will also be retrieved from CMS. Patients’ productivity loss (e.g. loss of work days due to doctors’ visits) will be self-reported. Their health-related quality of life will be assessed by the validated EQ-5D-5L at baseline, 6 months, and 12 months (needed for cost-effectiveness analysis if HealthCap is found superior to usual care; see under statistical method) [21].

Treatment adherence: This will be measured by the Treatment Adherence Questionnaire for patients with HT, which is validated in Chinese and contains measurements of adherence to medications, diet, stimulation, weight control, exercise, and stress reduction [22].

Self-efficacy: This will be measured using the validated 5-item self-efficacy scale specific to HT, which was found to have good internal validity (Cronbach’s alpha = 0.81) with a mean score of at least 9 (out of 10), signifying good self-efficacy [23].

Other physical parameters: Blood and urine tests will be collected at baseline and 12 months (serum creatinine, fasting glucose, HbA1c, and lipid levels [total cholesterol, total triglyceride, low-density lipoprotein, and high-density lipoprotein]), together with body mass index.

Satisfaction with HealthCap: All participants in the intervention group will be asked to rank their satisfaction with HealthCap and with the automatic drug refill process on a scale from 0 (completely dissatisfied) to 10 (completely satisfied) at 12 months. They will also be asked if they want to be recruited for an individual patient’s interview.

Acceptability: To assess the acceptability of the HealthCap system, around 30 patients with high (highest quartile score) and low (lowest quartile score) satisfaction will be invited for a patients’ interview until qualitative data saturation. Similarly, participating physicians (likely total number < 30) will be interviewed until qualitative data saturation if possible. Interviews will be conducted by the same trained research assistant face-to-face or by telephone. We will pilot test the patients’ interview guide on 2–3 patients prior to formal data collection.

Physicians will be asked about their experience of (i) introducing the HealthCap system to the patients, (ii) the drug auto-refill process and any relevant difficulties and concerns, (iii) a change in the doctor-patient relationship, (iv) any extra workload due to the use of the HealthCap system, (v) how HealthCap changes their usual practice and any perceived unmet patients’ health needs, and (vi) how likely that they will continue to promote and use the HealthCap system for these patients.

Similarly, patients randomised to use the HealthCap system will be asked about their experience with (i) a more frequent HBPM and self-management, (ii) any observed health changes and difficulties due to the HealthCap system, (iii) any unmet health needs during the last 1 year, (iv) the automatic drug refill process, (v) a change in the doctor-patient relationship, and (vi) how likely that they will continue to use the HealthCap system. The questions may be modified according to the quantitative results or any difficulty using HealthCap detected during the RCT. Data will be collected until saturation is reached.

Baseline data collection: Data on age, sex, marital status, educational level, smoking status (current smoker, ex-smoker, or never smoked), and alcohol use (assessed by the validated Alcohol Use Disorders Identification Test questionnaire) will be collected on recruitment [24]. Furthermore, eHealth literacy will be assessed using the validated Chinese 8-item eHealth literacy scale, which has high internal consistency (Cronbach’s alpha = 0.95) and has been used in Chinese with chronic diseases [25].

### Data collection and management

All research assistants who are involved in data collection will be trained in the correct use of instruments (e.g. ABPM) and questionnaires, as well as the retrieval of data. After each assessment, the files will be reviewed by research assistants to identify missing or erroneous data. Any missing information will be retrieved immediately from the instruments and the study participants. The data will be entered into the computerised database weekly or bi-weekly, depending on the recruitment rate. Data of participants at all timepoints will be collected even if they withdraw from the interventions, with their consent. The confidentiality of sensitive data (i.e. personal information) will be ensured by minimising the number of personnel who handle subject data. All data will be securely stored in password-locked computers and locked cabinets. For the questionnaire, data will be entered directly by patients online using research-grade software, Qualtrics. We will implement limits for responses to exclude impossible values, ensuring that the data is accurately captured in our database. All other data entries will undergo double data entry by two independent assessors to ensure accuracy and reliability. Each participant will be assigned a unique identification code for research data management. The code list can only be accessed by the research team and will be securely maintained by the principal investigator after the study is completed. Personal information will remain confidential throughout the study and will not be disclosed in future publications.

### Monitoring and adverse event management

There are no anticipated risks associated with the intervention. For participants using the HealthCap mobile app, index consultation will proceed as scheduled if BP is suboptimal or any of the safety questions screen is positive. HealthCap also has an automatic feedback function. For example, if BP is dangerously high (i.e. SBP ≥ 180 or DBP ≥ 110 mmHg), HealthCap will recommend a recheck and advise attendance at the emergency department if BP remains elevated.

In HK, all citizens have unlimited access to GOPCs and emergency departments for health problems. These services will not be limited for any participants in the current RCT. All participants are advised to seek medical help if BP becomes dangerously and persistently high (i.e. SBP ≥ 180 or DBP ≥ 110 mmHg) or in case of any suspected medical emergencies. In such circumstances, patients are asked to contact the study team at their earliest convenience. Any hospitalisations will be promptly reported to the relevant ethics committee within 24 h, or as soon as possible. Due to the low-risk nature of the study and that the funder did not allocate resources for a Data Monitoring Committee (DMC), this study will not have a DMC.

An interim report will be submitted by the principal investigator to the Health and Medical Research Fund, Hong Kong SAR, the funder of the current study only for its review and record (available at https://rfs1.healthbureau.gov.hk/english/funds/funds_hmrf/funds_hmrf_abt/funds_hmrf_abt.html). The report will include updates on the aims and objectives of the research, the timetable of work, and the achievements and major findings of the project to date. It will also detail expenditure and provide comments on the potential for disseminating research findings. Additionally, we will report on the recruitment rate, assess the balance between the two arms of the study, including any demographic imbalances that may be of concern, and report any interim results. Furthermore, we will document any trial-related adverse events and severe adverse events encountered during the study. The principal investigator will closely monitor participant safety during the study period. In the event of an adverse event, the principal investigator will review the case and report to the ethics committee for record and investigation. Although no harm to participants is expected from this study, we have consistently reported all severe adverse events to the ethics committee within 1 to 2 days of becoming aware of them. Should any concerns arise regarding the trial, the ethics committee has the authority to halt the trial at any time. Clinical trial insurance was purchased to cover compensation for participants who are harmed as a consequence of participation in this study. Financial auditing of the current study will be performed by the Chinese University of Hong Kong SAR.

### Sample size calculation

According to existing literature, a minimal clinically meaningful difference was set at an SBP difference of 2 mmHg [26]. By further setting type I error at 5% and type II error at 20%, and a standard deviation (SD) of 10 mmHg on ABPM (this is our primary outcome, and we observed this SD in our previous local studies) [27], the required sample size for this non-inferiority RCT will be 309. At the maximum dropout rate of 15%, 364 patients are required.

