## Methods

### Trial design and patient involvement

This protocol was written with reference to the Standard Protocol Items: Recommendations for Interventional Trials (SPIRIT) [11]. The SPIRIT checklist can be found in additional document 1. This is a parallel-arm RCT in which 364 patients with optimally controlled HT will be randomised in a 1:1 ratio to the HealthCap telemedicine (intervention) and usual care (control) groups and followed up for 12 months. For the primary outcome, we hypothesised that patients randomised to the telemedicine (HealthCap) group would have non-inferior BP control compared to patients allocated to the usual care group at 12 months. The RCT was pre-registered on clinicaltrials.gov (NCT06524180) and was approved by the Joint Chinese University of Hong Kong-New Territories East Cluster Clinical Research Ethics Committee (2023.525) and The University of Hong Kong/Hospital Authority Hong Kong West Institutional Review Board (UW25-086). The study complies with the Declaration of Helsinki.

Conducted during the peak of the COVID-19 outbreak in HK, the recruitment rate of the pilot trial was suboptimal for a main RCT (8 participants/month by 2 recruiting doctors) [9]. Thus, necessary modifications were made to ensure adequate recruitment in this trial.

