### Statistical analysis

The baseline characteristics of the participants in the two arms will be described using means with SD and proportions for continuous and categorical variables, respectively. The effect of the HealthCap telemedicine system on SBP measured by ABPM (our primary outcome) will be examined using analysis of covariance (ANCOVA) with baseline SBP measured by ABPM and the treatment group as the covariate, following the intention-to-treat (ITT) principle, that is, patients will be encouraged to conduct ABPM at 12 months regardless of whether they comply with the assigned intervention. A per-protocol (PP) analysis will be conducted for sensitivity analysis. PP analysis provides some protection for theoretical increases in the risk of type I errors (erroneously concluding non-inferiority). Our modified ITT (mITT) data comprised all patients according to and were included in the random allocation of complete data. We defined the PP population as participants who met the mITT definition but did not receive intervention treatments. Based on a previous meta-analysis, we set the non-inferiority margin for ABPM SBP at 2 mmHg [26]. We accepted the non-inferiority of telemedicine over usual care (in a 0.0125-level test after Bonferroni correction for multiple testing) if the lower bound of the two-sided 95% confidence interval (CI) (equivalent to the upper bound of the one-sided 97.5% CI) was within the non-inferiority margin. Subgroup analysis will be conducted in cases of unbalanced baseline characteristics and for patients with and without indications of a lower BP target (i.e. <130/80 mmHg). Additionally, missing data will be addressed through multiple imputation.

Qualitative data will be analysed by at least 2 investigators using inductive thematic analysis as described by Braun and Clarke [28]. Therefore, digital recordings will be transcribed verbatim. The recordings will be listened to several times, and the transcripts will be read and re-read by at least 2 investigators. After familiarisation, codes and then themes will be generalised. The investigator team will discuss the themes to determine and decide on any over-arching themes. The Consolidated criteria for Reporting Qualitative Research (COREQ) Checklist will be followed throughout the qualitative research part to ensure comprehensiveness and transparency in reporting qualitative findings [29].

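### On its stated inputs the required 309 is a per-arm number, but the protocol uses it as the trial total, so the stated 80% power does not follow

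*Protocol article*

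**What the plan says.** The Sample size calculation section of the protocol article gives these inputs:

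- Difference: "a minimal clinically meaningful difference was set at an SBP difference of 2 mmHg". The Statistical analysis section uses the same value as the margin: "we set the non-inferiority margin for ABPM SBP at 2 mmHg".
- Error rates: "By further setting type I error at 5% and type II error at 20" per cent. Whether the 5% is one-sided or two-sided is not stated.
- Variability: "a standard deviation (SD) of 10 mmHg on ABPM", attributed to previous local studies.

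The result is "the required sample size for this non-inferiority RCT will be 309. At the maximum dropout rate of 15%, 364 patients are required".

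That 364 covers both arms is clear from Trial design and patient involvement: "364 patients with optimally controlled HT will be randomised in a 1:1 ratio". The Abstract gives the same total, and Trial status counts recruitment as 114 of 365.

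The Statistical analysis section plans an ANCOVA on baseline ambulatory SBP. It judges non-inferiority by a two-sided 95% confidence interval, described as "equivalent to the upper bound of the one-sided 97.5% CI", and also names a 0.0125-level test. The article states no baseline to 12-month correlation, no variance reduction and no expected true difference for the sample size.

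**The concern.** The figure of 309 agrees almost exactly with the textbook unadjusted number per arm, yet it is inflated for dropout and split between two arms as if it were the total. If so, the trial has half the evaluable patients that its own inputs require.

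This matters because the Background justifies the trial by the need to confirm the pilot in an adequately powered RCT, and the cost-minimisation analysis is conditional on showing non-inferiority. A reader who takes the stated 20% type II error at face value would misjudge what a failure to show non-inferiority means.

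**Working it through.** **Inputs.** Margin 2 mmHg, SD 10 mmHg, type I error 5%, power 80%, dropout 15%, allocation 1:1, all from the article. The true difference is taken as 0 because the article states none. Normal quantiles: 1.645 (one-sided 5%), 1.960 (2.5%), 2.241 (1.25%), 0.842 (80% power).

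**Step 1: reproduce the stated figure.**

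n per arm = 2 × (z_alpha + z_power)² × SD² / margin²

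One-sided 5%: 2 × (1.645 + 0.842)² × 100 / 4 = 309.1 per arm.

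So 309 reproduces as a per-arm number (310 if rounded up), and only with the 5% taken as one-sided. It does not reproduce as a total at any of the three levels:

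| One-sided level | Per arm | Total evaluable | Randomised at 15% dropout |
|---|---|---|---|
| 5% | 309.1 | 618 to 620 | 728 to 730 |
| 2.5% | 392.4 | 786 | 925 |
| 1.25% | 475.3 | 952 | 1120 |

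**Step 2: how 309 is used.** 309 / 0.85 = 363.5, rounded up to 364, which is the two-arm total. Hence 364 / 2 = 182 randomised per arm and 309 / 2 = 154.5 evaluable per arm.

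**Step 3: power with 309 evaluable, unadjusted.**

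SE = 10 × √(4/309) = 1.138 mmHg, and power = Φ(2/1.138 − z_alpha).

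- One-sided 5%: Φ(1.758 − 1.645) = 54.5%
- One-sided 2.5% (the 95% interval rule): Φ(1.758 − 1.960) = 42.0%
- One-sided 1.25% (if the 0.0125 level is applied one-sided): Φ(1.758 − 2.241) = 31.4%

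The half-width of the 95% interval is 1.960 × 1.138 = 2.23 mmHg, wider than the 2 mmHg margin. The margin that could be excluded with 80% power at one-sided 2.5% is (1.960 + 0.842) × 1.138 = 3.2 mmHg.

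With no dropout (364 analysed), power is 60.4% at one-sided 5% and 47.9% at 2.5%.

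**Step 4: what ANCOVA could recover.** Treat SD 10 as the raw SD, so that the residual SD is 10 × √(1 − r²), where r is the baseline to 12-month correlation. For 309 in total to give 80% power:

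| One-sided level | Residual SD needed | r needed |
|---|---|---|
| 5% | 7.07 | 0.71 |
| 2.5% | 6.27 | 0.78 |
| 1.25% | 5.70 | 0.82 |

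Power with 309 evaluable for assumed values of r:

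| r (assumed) | One-sided 5% | One-sided 2.5% | One-sided 1.25% |
|---|---|---|---|
| 0 | 54.5% | 42.0% | 31.4% |
| 0.5 | 65.0% | 52.8% | 41.6% |
| 0.7 | 79.3% | 69.2% | 58.7% |
| 0.8 | 90.1% | 83.4% | 75.4% |

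**Step 5: a favourable true difference.** At one-sided 5% without adjustment, 80% power would need a true difference of 2 − (1.645 + 0.842) × 1.138 = −0.83 mmHg, that is, 0.83 mmHg in favour of telemedicine. The article assumes none.

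**The case against.** The primary analysis is not an unadjusted comparison. ANCOVA on baseline SBP can only help materially, so 54% and 42% lie at the low end, and they also assume the full 15% dropout, which the article calls a maximum. The pilot retained 98% over 6 months. At that rate about 357 would be evaluable, with unadjusted power of about 60% (one-sided 5%) and 47% (2.5%). A total of 309 would even be right at one-sided 5% if r were about 0.71. That per-arm and total were confused is an inference from the arithmetic; the article does not say how 309 was obtained.

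This stands as a limit on the size of the shortfall. It does not rescue the statement: the article claims no correlation, and 309 as a total does not follow from the inputs it lists.

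The pilot might also suggest a smaller SD. If its p = 0.41 for 128.2 versus 126.9 mmHg (n = 49) came from an ordinary two-group test with near-equal arms, the SE would be about 1.56 and the SD about 5.5 mmHg. With that SD, 309 evaluable would give about 94%, 89% and 83% power at the three levels. But the article does not name the pilot's BP method, follow-up was 6 months, the p-value may be adjusted, and the protocol itself chose 10 mmHg. This is a reason to check the SD, not support for 309.

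The same limits rule out a tempting reading in the other direction: taking the pilot's 1.3 mmHg as the true difference and concluding that power is very low. That difference is imprecise and cannot serve as the truth.

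**Conclusion.** The point holds in this form: the stated inputs require about 309 evaluable per arm, and the protocol provides about 155. The claim of 80% power therefore does not follow from the Sample size calculation section. Without covariate gain, power at a true difference of 0 is about 54% at one-sided 5% and 42% under the 95% interval rule. It would be about 31% if the 0.0125 level were applied one-sided.

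These figures rest on SD 10, 309 evaluable and no adjustment. They are not estimates of the power of the planned ANCOVA, which depends on a correlation that the article does not give.

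A reader might infer that failure to show non-inferiority is the likeliest outcome even if the two arms are truly equal. The documents do not support that as a general statement. It holds at one-sided 2.5% or stricter with weak or no adjustment, but not at one-sided 5% (54%), nor at an assumed r of 0.5 under the 95% interval rule (53%).

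The use of 5% in the sample size against 2.5% and 0.0125 in the decision rule is a separate inconsistency that needs its own reconciliation. Even at the most lenient of these levels the unadjusted total is short by half.

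**What to change.** In the Sample size calculation section:

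1. State that 309 is the number per arm for an unadjusted comparison at one-sided 5%.
2. Restate what 364 randomised (about 309 evaluable) delivers at the level used in the decision rule. Under the 95% interval rule without adjustment this is 42% power, or an excludable margin of about 3.2 mmHg with 80% power.
3. If the gain from ANCOVA is relied on, give the assumed baseline to 12-month correlation with its source, and base the calculation on SD × √(1 − r²).
4. Check the SD and the correlation on pooled data from participants already enrolled, without opening the allocation.

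The cost is revised wording in the protocol and registry record and one blinded check. The stated power becomes less favourable, but the correction itself needs no extra patients. Whether to change the target number is a separate decision for the sponsor and funder; recruitment was still under way when the article was written, so it can be taken in time.
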